#### Aim 2. Generate Data-Driven Insights to Improve Care Delivery Using Estimated MSMs

We will apply the estimated MSM parameters from aim 1 to generate inferences that yield actionable data-driven insights to improve care delivery for SUD. As shown in Table 3, these inferences fall into three general categories: (1) examine SUD care states and terminal event rates, (2) identify empirically common care pathways, and (3) identify the extent to which guideline-concordant care is achieved.

**Table 3. T3:** Summary of inferences from the multistate model and how they could be used by health systems to improve care for SUD^a^.

Key questions	Relevance to health systems	Analytic goal		
		Examine care states and terminal event rates	Identifies empirically common care pathways	Measure guideline-concordant care
How does the accessibility of reaching each care state vary?	Informs whether types of care are being reached at an expected rate, and whether resources are needed to support a given care type	✓		
How does the probability of occupying care states and terminal states vary over time?	Informs timing of interventions to address challenges in the delivery of SUD care	✓		
What are inefficient sequences of care following each initial state over time?	Identifies services or care patterns that need greater coordination (eg, multiple evaluations with delayed pharmacotherapy)		✓	
What is the contribution of each care state in achieving terminal states?	Prioritize SUD care types and inform places where specific SUD services are best delivered	✓		
What are the common (ie, most probable) sequences of SUD care following each initial state?	Helps health systems anticipate the needs of patients with SUD		✓	
How often and where is guideline-concordant care achieved?	Identifies care processes and locations to target for quality improvement			✓
How does the probability of occupying terminal states differ across patient subgroups?	Provides insights into whether outcomes differ for specific groups of patients who have incident SUD events in each setting	✓		
How do answers for the above key questions differ across patient characteristics?	Informs whether approaches to improve SUD care delivery should be tailored to different patient subgroups.	✓	✓	✓

a SUD: substance use disorder.

Table 4 summarizes estimates that can be obtained from fitted MSMs to generate our inferences and answer additional research questions. We will calculate point estimates and CIs and further characterize variation in output quantities across states graphically.

**Table 4. T4:** Summary of multistate model output quantities.

Output	Description	Example question answered
Intensity matrix	Instantaneous probability of moving from 1 state to another	How likely is a transition from an initial primary care state to a behavioral treatment and counseling care state over a small incremental unit of time?
Transition probability matrix	Probability of moving from 1 state to another over a specific time duration	What is the probability of moving from an initial primary care state to a behavioral treatment and counseling care state within 14 days of SUD^a^ identification?
Hitting probability	Point estimate of the probability of ever reaching a state	What is the probability of ever reaching pharmacotherapy during a care episode?
Mean sojourn time	Mean length of time a patient stays in a state	On average, how long does a patient stay in the evaluation and assessment care state before transitioning to another state?
Restricted mean transition-free time	Mean length of time a patient spends in transient states before reaching a terminal state	What is the average time before a patient ceases SUD care after receiving pharmacotherapy?
Expected first passage time	Expected days until hitting a specific state of a set of states	How long until a patient receives SUD pharmacotherapy?
Expected number of visits	Expected number of times a state is reached between 2 given times	What is the predicted number of times behavioral treatment and counseling are reached in the first 30 days of a care episode?
Survival plot	Probability of not reaching a state, as a function of time	How is the probability of not ceasing SUD care after their index SUD event?

a SUD: substance use disorder.

How does the accessibility of each state vary? We will use the models to describe how the accessibility of each state varies by estimating the dynamics of transitioning between different types of care for SUD. We will report and characterize variation in (1) transition probabilities, (2) hitting probabilities, (3) mean sojourn time, (4) expected first passage time, and (5) expected number of visits (definitions in Table 4).

How does the probability of occupying a given care state or terminal state vary over time? We will describe how the probability of occupying a state varies over time since cohort entry. To address this question, we will construct a stacked plot in which the y-axis represents the probability of being in each state, the x-axis shows time since cohort entry, and the stacked bands correspond to different states (Figure 2). Depicting the timing and probability of occupying states can help inform quality improvement interventions. For instance, by visualizing the time at which the probability of ceasing SUD care increases, it can help guide the timing of interventions to check for SUD care engagement and outreach to re-engage patients when needed.

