### Statistical Analyses

#### Aim 1: Apply MSMs to Comprehensively Characterize SUD Care Transitions

Separate MSMs will be run for each of the 5 subcohorts specified in Table 1. The 5 subcohorts are mutually exclusive. All prespecified states that are anticipated will be considered. States may be collapsed to address states with a small number of events, and new states may emerge if they occur with sufficient frequency (eg, concurrent receipt of pharmacotherapy and behavioral treatment and counseling). When collapsing or expanding states, we will strike a balance between clinical interpretability and reliable parameter estimation. As a general guideline, ≥40‐50 transition events from *S*_*j*_ to *S_j_* per covariate helps ensure stable hazard ratio estimates and corresponding SEs, but if collapsing states compromises the clinical interpretability of the results, we will adopt a more permissive threshold of at least 10 transition events per covariate for modeling [58]. This criterion will first be applied to define states; specifically, a minimum of 40 (or 10 under the more permissive threshold) transition events is required to define a state, allowing inclusion of 1 covariate in the transition model. When transitions are sufficient to include covariates in the model, at least 40 × *m* transition events are required. Covariate selection for each transition model, given the number of transitions, is described below. Follow-up time or care episode duration is defined as the interval from entry into the initial state (time 0) to entry into a terminal state.

Figure 1 provides a graphical representation of a simplified MSM illustrating potential care pathways. In this example, patients who meet the inclusion criteria and are identified as having an incident SUD in primary care enter the initial state *C*_1_. Patients then transit into 1 of 15 care states (*S*_1_, ... ,*S*_15_) defined by a service type and setting. From these states, patients may transition to temporary discontinuation of care, *D*, or an SUD remission state, *R*. Transitions between the transient states (care states, temporary discontinuation, and SUD remission) are bidirectional, whereas any transition to a terminal state (*T*_1_, ..., *T*_4_) is unidirectional, reflecting that patients cannot leave terminal states once they are entered in MSMs. At the end of follow-up, patients occupy 1 of the 4 terminal states.

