**Figure 2. F2:**
[figure not shown]
Stacked plot showing the probability of occupying specific care states or terminal over time (hypothetical). This hypothetical example shows the probability of ceasing SUD care increases steadily through day 15 and then plateaus through day 30, which could suggest a need for providing interventions to maintain engagement soon after a patient’s index SUD event. Over half of patients have ceased SUD care or have achieved SUD remission by day 45. SUD: substance use disorder.

What are inefficient sequences of SUD care following each initial state over time? Several inferences from the MSM may be a signal for inefficient SUD care. First, prolonged time in some states, such as inpatient care, may reflect challenges in coordinating care with services following an inpatient stay. We will thus identify states with relatively long mean sojourn time [67]. Second, care states with a low probability of being reached, or that take a long time before they are reached, may reflect barriers to care such as long wait times. To identify these care types, we will explore states with long expected first passage times [68] and low hitting probabilities [67]. We will also construct survival plots to display how the probability of starting in an initial access point (eg, index SUD event in primary care) and not reaching a target care state changes over time. For example, Figure 3 displays the probability of not reaching a target care state (eg, behavioral treatment and counseling in an outpatient setting) from different initial states. In this example, the probability of not reaching behavioral treatment and counseling in an outpatient setting following entry into the ED cohort is markedly higher than the corresponding probabilities following entry into the primary care or MHAC cohorts, suggestive of referral inefficiencies in ED services.

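### Expected first passage time, as Table 4 defines it, is infinite for any care state that some patients never reach, so it cannot compare accessibility or flag long waits

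*Protocol article*

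**What the plan says.** Table 4 (protocol article, Statistical Analyses, Aim 2) describes expected first passage time as "Expected days until hitting a specific state of a set of states". Its example question is "How long until a patient receives SUD pharmacotherapy".

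The Aim 2 paragraph on accessibility makes it one of five quantities to report and points back to the table: "4) expected first passage time, and (5) expected number of visits (definitions in Table 4". The Aim 2 paragraph on inefficient sequences takes "care states with a low probability of being reached, or that take a long time before they are reached" as possible signs of barriers to care, and continues: "To identify these care types, we will explore states with long expected first passage times". Low hitting probabilities are named in the same sentence.

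Under Aim 1 the terminal states are absorbing: "patients cannot leave terminal states once they are entered in MSMs". Every episode ends in one of them: "At the end of follow-up, patients occupy 1 of the 4 terminal states". Table 2 lists them as death, loss to follow-up, ceased care and administrative censoring.

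Two neighbouring quantities are bounded in time. Restricted mean survival time to a terminal state is taken over an interval fixed in advance, and the expected number of visits is counted between two stated times. First passage time has no such bound.

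**The concern.** A patient can be absorbed into death, ceased care or loss to follow-up before reaching pharmacotherapy or any other given care state. The plan expects this, since it reports hitting probabilities and looks for low ones. For such a patient the time to reach the state has no finite value, so an unrestricted mean over all patients does not exist as a finite number. The plan promises point estimates and confidence intervals for its outputs, and none can be given for this one as defined.

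At stake is one of the two quantities named for locating care types with access barriers. An analyst would have to choose a convention at the time of analysis, and the conventions do not agree. One obvious choice, averaging over those who reach the state, mixes the wait with the rate at which patients leave.

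**Working it through.** The article gives no numerical value for this quantity, so there is nothing to reproduce. It also gives no transition rates; all rates below are assumptions, shown over a range.

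**Set-up.** From the initial state, let the rate to the target care state be a per day and the rate to an absorbing terminal state be b per day, both constant.

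- Hitting probability: h = a/(a+b).
- Probability of not yet having reached the target by day t: S(t) = 1 − h(1 − exp(−(a+b)t)).
- Mean among those who reach it: 1/(a+b).
- Restricted mean time not yet in the target, up to τ, with terminal exits counted as not reached: τ(1−h) + h(1 − exp(−(a+b)τ))/(a+b).
- Cumulative incidence of reaching the target by τ: h(1 − exp(−(a+b)τ)).

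**Step 1: the quantity as defined.** The mean is the integral of S(t) over all t. S(t) falls only to 1 − h, so the integral diverges whenever h < 1. This does not depend on constant rates; it holds equally for the planned semi-Markov model. With a = b = 0.01, the integral up to τ is 0.5τ + 25(1 − exp(−0.02τ)):

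| Horizon τ (days) | 90 | 365 | 3650 | 36500 |
|---|---|---|---|---|
| Integral (days) | 65.9 | 207.5 | 1850 | 18275 |

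It is finite (1/0.01 = 100 days) only when b = 0, that is, when everyone reaches the state.

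**Step 2: faster exit (a = 0.01, b rising).**

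| b | h | Mean among reachers (days) | Restricted mean to 90 days | Reached by day 90 |
|---|---|---|---|---|
| 0 | 1.00 | 100 | 59.3 | 0.593 |
| 0.0025 | 0.80 | 80 | 61.2 | 0.540 |
| 0.01 | 0.50 | 50 | 65.9 | 0.417 |
| 0.04 | 0.20 | 20 | 76.0 | 0.198 |

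Access worsens down the table, yet the mean among reachers shortens. The restricted mean lengthens.

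**Step 3: slower entry (b = 0.01, a falling).**

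| a | h | Mean among reachers (days) | Restricted mean to 90 days | Reached by day 90 |
|---|---|---|---|---|
| 0.04 | 0.80 | 20 | 33.8 | 0.791 |
| 0.01 | 0.50 | 50 | 65.9 | 0.417 |
| 0.0025 | 0.20 | 80 | 82.8 | 0.135 |

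Here the mean among reachers moves in the right direction.

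**Step 4: the two side by side.** A mean of 20 days among reachers arises with a = 0.04, b = 0.01 (h = 0.80) and with a = 0.01, b = 0.04 (h = 0.20). The 90-day restricted means are 33.8 and 76.0 days, which separates them.

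**Step 5: a small network.** Three transient states (assumed rates 0.03 from the first to the second, 0.02 from the second to the third, 0.01 back) each have an entry rate to the target (0.01, 0.01, 0.002) and a common exit rate. Raising exit from 0 to 0.04 takes the hitting probability from 1.00 to 0.19 and the mean among reachers from 175 to 18.3 days. With exit at 0.01, cutting the target rates from four times to a quarter of those values takes the hitting probability from 0.77 to 0.15 and the mean from 21.1 to 68.1 days. Both directions are confirmed.

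**The case against.** The strongest reply has four parts.

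1. **Table 4 is a summary.** The method is cited, and the appendices and any analysis plan are not shown, so a horizon may be set there. This stands only in part. The article does more than stay silent: it states a definition, refers the reader to it, and that definition fails under the article's own absorbing states.

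2. **The companion measures already guard against a misreading.** Hitting probability is paired with first passage time in the same sentence. Survival curves for not reaching a target state are planned, Table 4 uses a 14-day transition probability as its example, and 7-day and 30-day probabilities are planned for follow-up after emergency care. This stands and lowers the importance of the point. It does not make first passage time finite. The article also does not say whether the curves count terminal exits as not reached.

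3. **The plan never says it will average only over reachers, and the direction of that mean is not fixed.** This stands. A reader might infer that worse access always looks like a shorter wait; Step 3 shows the opposite when entry is slow, which is the plain sense of a long wait. The exit pattern is also unknown. Ceased care requires more than 194 days without services. If it were dated at day 194 and were the only exit (an assumption), target rates of 0.02 and 0.005 per day would give hitting probabilities of 98% and 62%, and means among reachers of about 46 and 82 days, again in the right direction. The article does not say whether ceasing is backdated, and its hypothetical Figure 2 has ceasing rising through day 15, so neither pattern can be ruled out.

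4. **An infinite value reveals itself, and the study is exploratory.** Both are true. They argue for a lower grade, not for leaving the definition as it is.

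**Conclusion.** The point holds as a moderate correction. As defined, expected first passage time is infinite for every care state with a hitting probability below 1, whatever the rates, and so cannot rank states, settings or subgroups by wait. This rests only on the Table 4 definition and the absorbing terminal states.

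The size of any distortion in a mean among reachers rests on assumed rates. What can be said is that faster exit can make worse access look like a shorter wait, that slower entry lengthens it, and that this mean is therefore not a measure of wait alone.

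A reader might go further and infer that health systems will be told waits are short where access is worst. The documents do not support that: the conditional mean is not adopted, and the planned hitting probabilities and not-reached curves would show poor access. No primary endpoint or sample size rests on this quantity.

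**What to change.** In Table 4 and in the Aim 2 paragraphs on accessibility and on inefficient sequences:

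- Redefine the quantity as the restricted mean time not yet having reached the state, up to a prespecified horizon (for example 90 days). Count patients who enter death, ceased care or loss to follow-up as not reached.
- Report it with the cumulative incidence of first reaching the state by fixed days (for example 7, 14, 30 and 90), with those terminal states as competing events.
- Confirm that the planned not-reached survival plots use the same convention.
- If a mean among reachers is shown, label it conditional, print it beside the hitting probability, and do not rank states by it.

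The cost is a change of wording in one table and two paragraphs; the quantities come from the same fitted models by integration or simulation. The drawback is that results depend on the chosen horizon, so it should be fixed before analysis.

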**Figure 2. F2:**
[figure not shown]
Stacked plot showing the probability of occupying specific care states or terminal over time (hypothetical). This hypothetical example shows the probability of ceasing SUD care increases steadily through day 15 and then plateaus through day 30, which could suggest a need for providing interventions to maintain engagement soon after a patient’s index SUD event. Over half of patients have ceased SUD care or have achieved SUD remission by day 45. SUD: substance use disorder.

What are inefficient sequences of SUD care following each initial state over time? Several inferences from the MSM may be a signal for inefficient SUD care. First, prolonged time in some states, such as inpatient care, may reflect challenges in coordinating care with services following an inpatient stay. We will thus identify states with relatively long mean sojourn time [67]. Second, care states with a low probability of being reached, or that take a long time before they are reached, may reflect barriers to care such as long wait times. To identify these care types, we will explore states with long expected first passage times [68] and low hitting probabilities [67]. We will also construct survival plots to display how the probability of starting in an initial access point (eg, index SUD event in primary care) and not reaching a target care state changes over time. For example, Figure 3 displays the probability of not reaching a target care state (eg, behavioral treatment and counseling in an outpatient setting) from different initial states. In this example, the probability of not reaching behavioral treatment and counseling in an outpatient setting following entry into the ED cohort is markedly higher than the corresponding probabilities following entry into the primary care or MHAC cohorts, suggestive of referral inefficiencies in ED services.

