### States for the MSMs

States will capture 3 types of events related to SUD care: initial states, transient states, and terminal states. Defining states requires a balance of specificity to produce actionable information, and parsimony to allow for an estimable statistical model with accurate estimates and smaller SEs.

Initial states in the MSMs represent the clinical settings that triggered an incident event at the start of an SUD care episode, corresponding to the 5 subcohorts in Table 1.

There are 3 types of transient states. The first type is care states, which include different types of care provided in the health care system to treat the SUD, defined by combinations of setting and service type (Table 2). We opted to define 15 preliminary SUD care states based on a combination of 3 settings and 5 service types. The second type of transient state is temporary discontinuation of care. Entry into the temporary discontinuation care state is triggered using a clinically meaningful threshold for time elapsed between SUD treatment visits. The last transient state is SUD remission, which represents an improvement in the patients’ disease.

**Table 2. T2:** Transient states and terminal states are represented in the multistate models.

Category	States included	Description
Transient states	A total of 17 transient states include 15 care states derived from crossing 5 service types with 3 care settings; temporary discontinuation of SUD^a^ care; and remission of use disorder.	Care states Service types Evaluation and assessment Behavioral treatment and counseling Prevention, education, and case management Pharmacotherapy Other service Settings Outpatient Intensive outpatient Inpatient or residential Other transient states Discontinuation of SUD care A lack of SUD care over a specified period^b^ Remission of use disorder Low risk score on alcohol and substance use screen; clinically meaningful reduction on screening scores or <2 symptoms on *DSM-5*^c^ checklist; SUD remission diagnosis
Terminal states	4 states representing the end of a care episode	Death, derived from dates in health care enrollment records or Washington State death data Loss to follow-up, defined as at least 31 days without KPWA insurance coverages Ceased SUD care (no medication fills or services with a qualifying SUD diagnosis for more than 194 days Administrative censoring (in the middle of a care episode when data collection ends)

a SUD: substance use disorder.

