**Figure 1. F1:**
[figure not shown]
Graphical representation of the multistate model. Notation: Subcohort: [*C*_*1*_; care states (*S*_*1*_,...,*S*_*15*_); discontinuation of care: *D*; SUD remission state: *R*; terminal states: (*T*_1_,...,*T_4_*); *t*: time, *p*: probability] The 3 dots connecting the states indicate that the depicted relationships are possible for the other states not shown in this figure. p: probability; SUD: substance use disorder; t: time.

We will adopt a semi-Markov assumption [59] under which transition intensities depend on only the duration that patients spend time in the current state before transitioning. This framework allows transition intensities to vary over time rather than assuming constant transition intensities as in the Markov framework. Time is defined as the duration since entry into a state, with the clock reset to 0 upon entry into the cohort and each subsequent state. At any time since entry into the initial state, a patient occupies 1 of the 21 states (17 transient states and 4 terminal states). Movements between states *j* and *k*
$\left(j,k=S_{1},\ldots ,S_{15},D,R,T_{1},\ldots ,T_{4}\right)$, are governed by a 21-by-21 matrix of transition intensities $q_{jk}(t,z(t))$, which is a function of time *t* and covariates z(t). Intensities capture the instantaneous probability of moving from state *j* to *k*.

Under the semi-Markov assumption, we will fit separate flexible parametric survival models [60,61] for each transition:

$\log\{q_{jk}(t,z(t))\}=s(\log(t)|\eta ,k_{0})+\beta^{T}z_{i}(t)$.

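### Mean time in an inpatient or residential state mixes length of stay with a capped post-discharge wait, so it cannot by itself signal poor coordination after the stay

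*Protocol article*

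**What the plan says.** In the Aim 2 paragraph on inefficient sequences of care, the protocol article states that "prolonged time in some states, such as inpatient care, may reflect challenges in coordinating care with services following an inpatient stay". It continues: "We will thus identify states with relatively long mean sojourn time". Table 4 defines mean sojourn time as "Mean length of time a patient stays in a state".

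The states are set out in States for the MSMs and Table 2: "A total of 17 transient states include 15 care states derived from crossing 5 service types with 3 care settings", plus temporary discontinuation and remission. Under Aim 1 of the Statistical Analyses, "At any time since entry into the initial state, a patient occupies 1 of the 21 states", and the clock returns to zero at entry to each state. Entry to temporary discontinuation is "triggered using a clinically meaningful threshold for time elapsed between SUD treatment visits". Footnote b to Table 2 sets that threshold separately for each care state, always below 194 days, but gives no values. The Health Care Encounter Data section takes transition times from visit timestamps and does not name discharge as an event.

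**The concern.** A hospital or residential stay has a length, and the wait for the next service starts when it ends. The planned signal is meant to say something about the wait. The state list gives the patient nowhere to be during that wait except the state just left, at least until the discontinuation threshold is reached. Mean sojourn then adds the two durations together.

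Table 3 uses inefficient sequences to show health systems where care needs more coordination. A state could be flagged because its stays are long although follow-up is prompt. Another could escape notice because its stays are short although the gaps afterwards are long. Expected first-passage times counted from entry to an inpatient state carry the same mixture.

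**Working it through.** **1. State count.** 5 service types × 3 settings = 15 care states. Adding discontinuation and remission gives 17, and adding 4 terminal states gives 21. This matches the article. None of the 21 means discharged and awaiting the next service.

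**2. Where a discharged patient can be.** Take a patient with no new service, no remission and no terminal event, whose gap is still below the threshold. Discontinuation, remission, the terminal states and any new care state are all excluded, so only the inpatient or residential state last occupied is left. Occupancy ends at the first of: next service, threshold, remission, terminal event.

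**3. The other reading.** Suppose occupancy ended at discharge. The patient would then be in no state until the next event, against the statement that one of the 21 is always occupied. Sojourn would be length of stay alone and would contain no time after the stay.

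**4. Illustration.** The article supplies none of these inputs, so all are assumptions:
- L: days in the last-occupied inpatient state up to discharge
- W: post-discharge wait, exponential with mean w
- c: discontinuation threshold in days, counted from discharge

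Remission and terminal events are ignored. Then
- mean sojourn = L + w(1 − exp(−c/w))
- P(exit to discontinuation) = exp(−c/w)

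Case A has L = 28 and w = 5. Case B has L = 7, with w solved so that its mean sojourn equals that of A. At c = 60:
- A: 28 + 5(1 − exp(−60/5)) = 33.0
- B: 7 + 30.1(1 − exp(−60/30.1)) = 33.0

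| c (days) | A: mean sojourn | B: mean wait giving the same sojourn | P(to discontinuation), A | P(to discontinuation), B |
|---|---|---|---|---|
| 7 | 31.8 | none; B cannot exceed 7 + 7 = 14 | 0.247 | – |
| 14 | 32.7 | none; B cannot exceed 7 + 14 = 21 | 0.061 | – |
| 30 | 33.0 | 101.9 | 0.002 | 0.745 |
| 60 | 33.0 | 30.1 | 0.000 | 0.136 |
| 90 | 33.0 | 27.0 | 0.000 | 0.035 |
| 193 | 33.0 | 26.0 | 0.000 | 0.001 |

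**5. Reading the table.** With a short threshold the wait adds at most c days, so sojourn mostly ranks length of stay. From 30 days upward, equal sojourns can hide mean waits of 5 days and of 26.0 to 101.9 days. The probability of exit to discontinuation separates the two cases clearly at 30 days, weakly at 90 and hardly at all at 193.

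**The case against.** The case for the plan has several parts.

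- **The mechanism is inferred.** No sentence says that discharged patients are kept in the inpatient state. The care states are called preliminary, new ones may emerge, and coding details may stand in appendices or a fuller plan not shown. This stands as a caveat. But the alternative in step 3 does not rescue the signal, because sojourn would then hold no post-discharge time.
- **The wait is capped.** A reader might infer that a discharged patient stays in the state until the next service, however long that takes. The documents do not support this: discontinuation, remission and the terminal states also end occupancy.
- **Other outputs carry information.** A reader might infer that the inpatient-to-outpatient handover cannot be estimated at all. That goes too far. Transition and hitting probabilities are planned, cycling between inpatient and outpatient care does not need a discharge clock, and inpatient-to-discontinuation transitions partly show failed handover. The article nevertheless attaches the coordination reading to sojourn.
- **The 7- and 30-day follow-up measure is untouched.** It applies to patients whose incident event is in an emergency department and runs from the initial state. The article shows no such window for patients leaving residential care.
- **There are five inpatient or residential states.** A change of service type within one stay resets the clock, so sojourn in one state need not be the whole stay plus wait. The mixture then sits in the last state occupied.
- **States are compared, not programmes.** That is correct. Cases A and B show how sojourn behaves and are not a comparison that the plan makes.
- **Long stays can themselves reflect poor coordination**, for example when discharge is delayed because no later service is ready. This is a fair reading and a reason to keep length of stay as its own output. It does not make the combined figure interpretable.

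The wording is also cautious (long time *may* reflect a problem) and the study is exploratory. This lowers the stakes but leaves the signal as planned.

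**Conclusion.** The concern holds in a limited form. On the stated 21-state partition, mean sojourn in an inpatient or residential state is time up to discharge plus a post-discharge wait, cut off at the discontinuation threshold (under 194 days), remission or a terminal event. Alone, it cannot carry the reading that long inpatient time reflects poor links to later services. In the assumed illustration, a sojourn of 33.0 days fits mean waits of 5 and 30.1 days at a 60-day threshold, while at 7 or 14 days the figure is driven mainly by length of stay.

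The conclusion rests on the literal state list. The size rests on assumed stays, waits, thresholds, an exponential wait and a threshold clock starting at discharge; the article does not say whether it starts at admission or discharge. The defect concerns the interpretation of one planned output and does not make the model as a whole invalid. It should be corrected before inpatient sojourn is reported as a coordination signal.

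**What to change.** Assuming discharge dates are available in the encounter and claims data:

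- For inpatient and residential care, report length of stay and time from discharge to next SUD service as two quantities.
- State that the discontinuation threshold for these states is counted from discharge.
- Base the post-stay coordination signal on discharge-to-next-service time together with the inpatient-to-discontinuation probability, not on mean sojourn alone.
- Keep long stay, if wanted, as a separate signal, for example of delayed discharge.

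The cost is some recoding and one extra descriptive output.

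A separate transient state for patients discharged and awaiting their next service is optional. It could add up to 5 entries and 15 + 2 + 4 = 21 exits in each of the five subcohort models. It should be used only where the plan's guideline of 40 events, or 10 under the permissive rule, allows.
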